### 8.12.2 Pre-screening

Parents / guardians of children who fulfil the pre-screening eligibility criteria will be informed about the study by the hospital or study staff. Consent will not be obtained at the acute stage of the illness but a few hours or days later when the child has recovered and is able to take oral medication and discharged. This provides a time window for the parents or guardian to reflect on the study and discuss it with family members and study staff.

Pre-study screening will be done by hospital staff or study staff. No study specific information or study samples will be collected in this pre-study screening period. However, study staff may be asked to keep any leftover blood volume of routine samples that would otherwise be discarded (e.g. for blood-group typing and cross-matching) in the fridge until consent is obtained at enrolment. The role of the study team during this period is to review the diagnosis and ensure that the potential study participants get standard care for severe malarial anaemia.

Each pre-screened subject will be assigned a pre-screening number in sequential order by the hospital regardless of whether they fulfil the pre-screening eligibility criteria. Data will be recorded on a pre-screening log that will be kept in the investigator's site file. This record will be used to report how many patients were pre-screened and how many were eventually recruited in the study to establish that the study population was selected without bias. This screening log will not contain names or other identifying information.

### 8.12.3 Screening interview and consent & Enrolment

#### 8.12.3.1 Screening & Consent

The parents of the children will be approached for a screening interview as soon as the child is sufficiently recovered to take oral medication (i.e. after completion of the blood

transfusion and the standard parenteral artesunate medication [if any is indicated]). This is typically within 24 to 48 hours following admission to the hospital. During this interview, consent will be sought from the parents or guardian and if consent is granted, the eligibility criteria for inclusion into the study will be assessed.

#### 8.12.3.2 Screening log

The investigator will keep a subject screening log for all subjects considered for enrolment regardless of whether they were enrolled, which, combined with the pre-screening log will be used to establish that the study sample was selected without bias. This screening log will not contain names or other identifying information.

#### 8.12.3.3 Assignment of study IDs

Eligible subjects will be issued a study subject number during the enrolment visit. Once issued the study subject number they will be considered as 'enrolled.' This number is the subject's unique identifier and used to identify the subject on the CRFs. Subject numbers will be assigned strictly sequentially as subjects enter the study depending on the cluster the participant will be coming from. Once a number has been assigned no attempt will be made to use that number again, for example if a subject discontinues or is a screening failure. Study participants will be randomised to study arms depending on the cluster from which they come from.

#### 8.12.3.4 Clinical assessment:

After consent is obtained and the subject's eligibility is confirmed, the subject's demographic data will be recorded in the CRF, and all relevant clinical information, including the previous and current medical history, and laboratory information copied from the hospital's clinic and laboratory notes to the CRF (see CRF for details). A further clinical examination (including anthropometrics) will be performed and a medical history taken that will serve as the baseline examination and captured on the CRF.

#### 8.12.3.5 Baseline Laboratory Measurements

*As part of standard of care:* Children with severe anaemia are expected to have the following tests done as standard of care before blood transfusion: Malaria smear or RDT, haemoglobin concentration, blood smear to type the anaemia, blood cultures (if patient is febrile and facilities are available), complete blood count haemogram (subject to availability of automated analysers). In addition they are expected to have a blood group and cross match test with donor blood as part of the blood transfusion process. After completion of the blood transfusion, a post transfusion haemoglobin concentration is taken. If the patient was suspected to have malaria, a repeat malaria smear or RDT is often taken to evaluate whether the parasitemia has been cleared.

We shall record all these laboratories results and any others tests results such as urinalysis and radiological results that might have been done as part of standard of care. During the pre-study screening period the study team shall support the hospital to facilitate the routine use of these tests and the recording of clinical and laboratory information on the clinical and laboratory forms and hospital registers to ensure they are available to the study team once the patient is enrolled into the study.

*Study specific samples:* In addition to the standard of care tests, a venous blood sample will be taken (3 ml) through the existing cannula where possible (in which case no additional 'prick' will be required). In cases a sample cannot be collected through the existing cannula, a finger prick will be performed. This will be used for checking malaria

parasites using microscopy, haemoglobin and a DBS sample on filter paper for genotyping of malaria parasites

*HIV testing or collection of information on HIV-exposure* (i.e. maternal HIV status) will not be done as a study specific procedures, but the information will be copied from the clinical and laboratory hospital records of patients, including information on the maternal HIV status, where available, or the HIV-status will be obtained following provider initiated testing and counselling (PITC) procedures that are part of routine in-hospital care. Where required the study will support the hospital infrastructure needed to generate this information for the study to ensure this information is available for all study participants.

#### 8.12.3.6 Location of household and issuance of study ID card

A detailed route description to locate the participant's household, including sketching a map, if needed, will be recorded, to aid the planned PMC treatment follow up visits at home. Lastly, a subject's identification card will be issued. A GPS will be used to collect the exact location of the participant's house.

#### 8.12.4 1st, 2nd and 3rd PMC treatment schedules

The 1st, 2nd and 3rd PMC treatment will be given 2, 6 and 10 weeks following enrolment. These treatments will be given at home for those randomised to Arm 1, 2 or 3 and at OPD for those randomised to Arm 3 and 4 (Day 1 dose only, Day 2 and 3 will be at home). PMC uptake will be assessed by unannounced visits on day 4 or 5 after each treatment course by a research assistant. If children are found to be ill during these home-visits they will be referred to the study clinic for further evaluations as part of the unscheduled visits as described below.

#### 8.12.5 Study end visit

Study participants will be asked to return to the study clinic at the hospital at 15 weeks. At this visit a history will be taken and examination performed. A blood sample will be taken for malaria slides, haemoglobin and DBS for malaria parasites genotyping. Additional treatment for malaria and / or anaemia will be given if required. Study staff will visit the house if the family fails to present for this visit at the clinic.

Economic costs will be identified from the patient perspective by asking whether the patient sought any medical treatment, other than at Zomba Central Hospital, during the trial period. If so, costs of travel time, waiting time and associated costs will be identified. In addition, patient intervention costs of time spent receiving the treatment will be identified and any additional costs associated with this, such as special dietary requirements, among others.

#### 8.12.6 Unscheduled visits (passive follow-up)

##### 8.12.6.1 Inter-current illness

A passive surveillance system will be used to monitor inter-current illnesses through study-clinics. Parents will be instructed to bring their child to the study clinic for any suspected illness. The 'chief complaint' (reason for attending the clinic during passive surveillance) and 'diagnosis' will be recorded using a standard list based on the International Classification of Disease (ICD-10) for children[18]. Blood samples for malaria smears, parasite genetics (filter paper dried blood spots) and haemoglobin will be taken if clinically indicated (e.g. documented fever  $\geq 37.5$  °C axillary or  $>38.0$  °C rectal, or a history of fever in the last 24 hours).

#### 8.12.6.2 Verbal autopsy visit

All parents of children who die will be visited at home as soon as possible for a detailed verbal autopsy interview using standardized questionnaires that will be used to categorize the potential cause of death as probable, possibly, or not malaria related.

## 9 SUB-STUDIES

### 9.1 ECONOMIC EVALUATION

The economic evaluation will provide information about incremental costs, incremental health benefits and cost-effectiveness of different delivery strategies of PMC compared current standard of care in Malawi. The overall aims are to inform decision makers whether PMC is likely to be cost-effective if routinely implemented, and which delivery strategy that is likely to be most cost-effective.

A novel decision-model (Fig 2) will be developed to capture aspects relating both to treatment efficacy and relating to country specific implementation characteristics including different implementation costs. Since recurrent follow-up is common, and since previous health events are risk factors for new events, a micro-simulation model is adequate to capture costs and health outcomes. The influence of single parameters will be analysed with one-way sensitivity analyses, while overall decision uncertainties will be estimated utilising probabilistic sensitivity analysis. Incremental costs will be calculated per case averted of severe anaemic malaria, per death averted and per disability adjusted life year (DALY) averted. Treatment efficacy will be based on primary data from this trial, combined with results from the previous RCT in Malawi [2] DALYs will be calculated using standard assumptions from the recent Global Burden of Disease Study.

**Figure 2:** Decision Model

[figure not shown]

The interventions will be costed prospectively from the perspectives of both the health care provider and the patients/families. Costs will be calculated from a societal perspective, but results will be presented disaggregated for the health care provider and

the patients/families. We will use an ingredients approach, in which resources in separate processes are identified, quantified and valued.

The economic evaluation requires collection of some data in addition to the implementation trial data. The families of the affected children face cost related to receiving the PMC treatment (intervention costs), and in addition they are subject to costs related to the primary disease, readmissions or death (disease costs). Likewise, the health care providers need resources to provide the intervention, which in turn will affect future cases of disease.

#### **9.1.1 Patient intervention costs**

The patients' costs of receiving the intervention will be considered in the final study visit. A number of questions will be asked to assess the additional direct and indirect costs associated with receiving the PMC intervention, including travel expenses, treatment expenses and time use for care-takers. Only costs occurring post-discharge will be considered as intervention costs. Time use will be valued assuming that national minimum wage rates represent the alternative cost of the care-takers time.

#### **9.1.2 Patient disease costs**

Patients face costs relating to treatment of the primary disease and anaemia, as well as re-admissions or death. Patients' expenses and time use related to the primary disease will be assessed during the enrolment visit or at discharge from the hospital, while their costs related to recurring cases of disease will be considered during the unscheduled sick visits to the study clinic. Both tradable and non-tradable cost items will be identified, measured and valued. Household economic outcomes will be estimated as in the Living Standard Measurement Surveys ([www.worldbank.org/lsms](http://www.worldbank.org/lsms)).

#### **9.1.3 Provider intervention costs**

Provider costs of implementing the five different modes of PMC will utilize information from project accounts, as well as interviews with program managers and health care staff. The data collection will be done retrospectively towards the end of the clinical trial, and efforts will be made to separate intervention costs from costs related to research activities.

#### **9.1.4 Provider disease costs**

The assessment of disease treatment costs from the perspective of the health care provider will combine data from facility records and accounts, interviews with health care workers in the hospital and patient cards, and will capture direct and indirect health care provider, capital and recurrent costs. The primary disease and anaemia will be costed prospectively for the recruited children, while re-admissions will be costed prospectively after discharge of patients for all cases retrospectively.

It is increasingly being acknowledged that societal costs are essential in cost-effectiveness analysis; the World Health Organization also recommends this for all analyses conducted. A broader societal perspective is important because the disease not only inflicts costs on the healthcare system, but also puts considerable burdens on the household when an individual falls ill. For the patient there are direct out-of-pocket expenses associated with expenses related to seeking preventive treatment as well as

treatment of re-admission. In addition, the indirect costs related to the value of the time loss spent seeking the treatment both for the patient and the care-taker represent a burden that can be even larger than the directed expenses. Specific objective 5, is thus very important for the analysis as it means including the perspective of the households/patients/families, who are the main benefactors of the intervention. In the following, we will therefore attempt to explain better the costing methods and argue that sub-objective 5 is achievable.

Numerous studies on care seeking costs and the following burdens have been conducted. One relevant example that indicates the feasibility of such measurements is Ewing et al [19]; they conducted a costing study of treatment-seeking and household cost of febrile illness among children in Malawi. This article is co-authored by [name]. Additionally, [name] has vast experience in conducting costing studies where the patient perspective is also considered; see f.eks. Ngalseoni et al [20] and Wandwalo, [name] and Morkve [21]. Recent experience from Kisumu, Kenya, where another branch of this study is taking place, demonstrates that mothers easily and willingly answer questions about their time use and expenses related to seeking care for malaria disease.

## **9.2 EQUITY IMPACT ANALYSIS**

In addition to important components such as cost-effectiveness, safety and efficiency when considering delivery mechanisms, a consideration of equity is equally valuable. In health we are concerned with its distribution within the population; equity is a term that captures the moral and ethical concern for this distribution. Does delivery mechanism affect compliance based on different socioeconomic variables? Is a specific mechanism superior for a specific part of the population depending on socioeconomic factors or positions? Does one of the delivery mechanisms secure better equity compared to the others? In order to resolve these issues, it is important to detect which determinants, if any, is imperative for the delivery of PMC. This is an effort to incorporate equity into cost-effectiveness, and will be valuable input to decision makers when considering new policies.

In order to conduct an equity impact analysis, an asset index has proven valuable; this is particularly so in areas where income levels might be difficult to define or differentiate by socio-economic group. The analysis can be done by dividing the population into quintiles, based on possession of assets in the household, such as: building materials (in house), water source, radio, bicycle, livestock, acres of land, cooking fuel, food items etc. This information will be collected during the study-end visit.

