## 8.3 SAMPLE SIZE

Although a factorial design will be used, only the main effects of PMC mode of delivery and the “use of SMS/HSA reminders” are of primary interest. There are five arms in total as described above such that each of the four intervention arms will be compared to the control arm (Arm 1: Mother given at discharge without SMS reminder). Each village cluster contributes 2 to 4 children/year on average with severe anaemia. Thus, the cluster sizes vary and we have accounted for this in sample size calculations in order to achieve the number of clusters that would have enough power to detect the desired difference. The sample size calculation has been adjusted in the design effect using the coefficient of variation method [11-13]. This has assumed that the cluster sizes will be uniformly distributed between 2 and 4 children i.e. U[2,4]. This gives a mean cluster size of 3 children per village per year and a standard deviation of cluster sizes of 0.58. Hence the coefficient of variation of cluster sizes (CV) is  $0.58/3 = 0.19$  and  $CV^2 = 0.036$ . Assuming an

intra-cluster correlation coefficient (ICC) of 0.1 and allowing for 10% loss-to-follow-up, a sample size of 25 clusters of an average of 3 children per village (75 children per arm, N=375 overall (for 125 clusters for the 5 arms)) has 80% power to detect a 25% absolute increase in uptake from an estimated 50% in the OPD and delivery at home groups to 75% in the arms supported by SMS reminders ( $\alpha=0.05$ ). The ICC of 0.1 is slightly more conservative than the ICC in a previous trial of delivery approaches for IPTc in the Gambia (0.08)[14].

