## 8.12 PARTICIPANTS TIMELINE

### 8.12.1 Overview Study Phases

The study plan and schedule of assessment is provided Table 2: Study Design and Schedule of Assessment.

It consists of an in-patient pre-study screening period while the patient is acutely ill (approximately -4 to 0 days before enrolment) followed by a screening and enrolment at discharge. It will be during this enrolment visit when the children become formal study participants ( $t=0$ ). They will also be provided with artemether-lumefantrine (AL) (Coartem®) during the time they in hospital.. During enrolment visit (at discharge), the child will be allocated to one of the 5 study arms. Depending on the arm the mother and child will either return to OPD clinic for PMC drugs at 2, 6 and 10 weeks or be given at discharge to administer them at home also at 2, 6 and 10 weeks. The subjects (a subset) will be visited again at home at 2, 6 and 10 weeks after enrolment to assess DHA uptake for each PMC treatment course. These home visits will be for adherence check purposes, vital registration and health economic assessments only, not for clinical assessment. The PMC period ends at 14 weeks, i.e. 4 weeks after the third PMC course. They will then be requested to come to the clinic at 15 weeks after enrolment for an end of study assessment. Subject's parent or guardian will be instructed to return his/her child to the study clinic for evaluation free of charge at any time their condition warrants medical attention during the 14 weeks follow-up period after discharge.

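### The asset index for the equity analysis is collected at study end rather than at enrolment, and the protocol contradicts itself on when patient intervention costs are taken

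*Protocol*

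**What the plan says.** **Asset index.** Section 9.2 poses the question "Does delivery mechanism affect compliance based on different socioeconomic variables" and proposes quintiles built from household possessions such as building materials, water source, radio, bicycle, livestock, land, cooking fuel and food items. On timing it says: "This information will be collected during the study-end visit". Section 8.5 mentions socioeconomic household features among variables taken at enrolment and follow-up, but names no asset items and assigns no visit.

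**Patient intervention costs.** Section 9.1.1: "The patients' costs of receiving the intervention will be considered in the final study visit". Section 8.12.5, on the study-end visit: "In addition, patient intervention costs of time spent receiving the treatment will be identified and any additional costs associated with this". The patient-costs row of Table 2 is marked at visit #1 and visit #5 only. Section 8.12.1, however, says "The subjects (a subset) will be visited again at home at 2, 6 and 10 weeks after enrolment" and adds: "These home visits will be for adherence check purposes, vital registration and health economic assessments only, not for clinical assessment".

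**Timing and tracing.** The end visit is at 14 weeks in the note to Table 1 and in Table 2, and at 15 weeks in Sections 8.7.6.2, 8.12.1 and 8.12.5. If a family does not attend, Section 8.12.5 has staff go to the house, and Section 8.7.6.2 offers calls, transport and a possible evaluation at home. Families of children who die have a verbal autopsy interview (Sections 8.7.5.2 and 8.12.6.2), with no asset or cost items mentioned.

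**The concern.** The equity question concerns effect modification: does the difference in compliance between delivery modes vary with household wealth? The modifier should be fixed before the intervention and known for everyone randomised. Section 9.2 measures it once the outcome is complete and only in families who can still be reached. Those who cannot be reached may well differ in both wealth and compliance, which are the two quantities the analysis relates. A few of the listed assets, livestock and food items in particular, could also change over 14 or 15 weeks in a household dealing with a sick child.

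For costs, staff cannot tell from the protocol whether to ask about trips and time at the home visits or at the end. The choice matters unevenly between arms. Arms 4 and 5 have three drug-collection trips to recall and Arms 1 to 3 have none, so error in recalled fares and travel time would fall on one side of the comparison that specific objective 5 calls for.

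**Working it through.** The protocol states no recall length and no expected missingness for the asset index, so there is no figure to reproduce. Two quantities follow from its schedule and its loss allowance.

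**1. Recall of intervention costs at the end visit.** Inputs: courses at days 14, 42 and 70; end visit at week 14 (day 98, Table 2) or week 15 (day 105, Section 8.12.5). Recall in weeks = (end-visit day − course day) / 7.

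- Course 1: (98 − 14)/7 = 12.0; (105 − 14)/7 = 13.0
- Course 2: (98 − 42)/7 = 8.0; (105 − 42)/7 = 9.0
- Course 3: (98 − 70)/7 = 4.0; (105 − 70)/7 = 5.0

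Using the Table 2 windows (day 14 ± 3, day 98 ± 7), the longest interval for course 1 is 105 − 11 = 94 days, or 13.4 weeks. Had the questions been asked at a spot check on day 4 or 5 of the course (Section 8.9.1), the interval from the first dose would be 3 to 4 days.

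**2. Who could lack an asset index.**

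- Ceiling from the plan's allowance: Section 8.3 sets the sample size "allowing for 10% loss-to-follow-up". 0.10 × 375 = 37.5 children, or 0.10 × 75 = 7.5 per arm. This would apply to the index only if every such loss had occurred by the end visit and no home visit succeeded. For scale, a quintile of 375 children is 75.
- Deaths: Section 6.1 gives 8% by 6 months after discharge in an earlier study. The share by week 14 or 15 is not in the protocol. Assuming 2% to 8%, the number is 0.02 × 375 = 7.5 to 0.08 × 375 = 30 children. The upper end is a 6-month figure and so is probably too high here.
- Loss avoidable by timing alone: uptake is complete at the third spot check, on day 4 or 5 of a course starting on day 70, that is day 73 or 74. The end visit follows 98 − 74 = 24 to 105 − 73 = 32 days later. A child who dies, withdraws or moves away in that interval has known uptake but no asset index. The protocol gives no rate for this group.

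**3. The cost passages side by side.** Section 9.1.1 counts only post-discharge costs as intervention costs. The visit #1 mark in Table 2 therefore cannot cover them: Section 9.1.2 uses enrolment or discharge for primary-disease costs. Table 2 thus leaves intervention costs to visit #5, in line with Sections 9.1.1 and 8.12.5. Section 8.12.1 points to the home visits instead, in a subset, and Section 8.1.2 also limits the economic evaluation to a subset. The note under Table 2 places the home visits at weeks 6, 10 and 14, whereas Section 8.12.1 has weeks 2, 6 and 10. The time of the home interview is therefore unsettled too.

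**The case against.** Several stronger readings are tempting, and the protocol does not support them.

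- A reader might infer that costs are taken at the end visit and nowhere else, so that long recall is settled. Section 8.12.1 contradicts that. If it governs, most of the recall problem disappears in the subset visited. What can be asserted is a contradiction, together with the recall that applies if the final-visit passages govern.
- A reader might infer that every family missing the clinic visit is lost to the equity analysis. Sections 8.7.6.2 and 8.12.5 provide for home follow-up, so what remains is death, withdrawal and families who cannot be traced.
- A reader might divide the 10% allowance by the expected share of non-completers and conclude that the index is missing for 20% (10/50) to 40% (10/25) of them. That treats a sample-size allowance as loss at the end visit and assumes that every lost child is a non-completer. Nothing in the protocol supports either step.

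Other objections stand in part. A child lost before the third spot check also has incomplete compliance data, so an enrolment asset index would not by itself bring that child into the analysis. Most listed assets are unlikely to change in 14 or 15 weeks, and no effect on quintile rank is shown. Section 8.5 may intend some socioeconomic data at enrolment, though Section 9.2 is the specific instruction. Asking about trips after courses 1 and 2 could act as a prompt for later attendance, and attendance bears on the primary outcome.

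These objections limit the size of the problem. They do not give a reason to measure a baseline modifier last.

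**Conclusion.** The point holds for the asset index as a matter of timing. Section 9.2 fixes a baseline modifier at week 14 or 15, and no passage secures it for children who die, withdraw or cannot be traced. The number affected cannot be derived from the protocol. It is at most 37.5 of 375 if the 10% allowance is right and no home visit succeeds, and fewer to the extent that home visits succeed. An analysis plan cannot recover assets that were never recorded, so this has to be settled in the protocol.

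For patient intervention costs the finding is an internal contradiction. If the final-visit passages govern, recall is about 12-13, 8-9 and 4-5 weeks for the three courses, and the burden of recalling trips falls on Arms 4 and 5.

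Only the secondary cost analysis and the equity analysis are affected. The primary outcome comes from the spot checks and is untouched.

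**What to change.** **Asset index.** Move the existing asset questions to visit #1, where Table 2 already has a patient-cost item. Define the quintiles from those answers and amend Section 9.2 to match. The index is then available for children who later die or are lost, and for families who stop taking part but leave their earlier data usable (Section 8.8). The cost is a few more minutes at enrolment.

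**Patient costs.** Reconcile Sections 8.12.1, 8.12.5 and 9.1.1, the patient-costs row of Table 2 and its note on home visits. State when intervention costs are asked, in whom, and whether the end visit is at week 14 or 15. Where home visits are made for the economic sub-study, record trip costs and time there, with the same questions in all five arms, and keep the end visit for the remaining items. This adds a few minutes per visit. It carries a small risk that the questions prompt attendance at later courses, which the protocol should acknowledge. Extending the cost questions to every child would be a further decision, because Section 8.12.1 foresees them only in a subset.
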